### Data collection procedures

Protocols and publications will be collected for each of the RCTs and the cost data will be collected and stored in the electronic data capture system REDCap [33, 34]. Trial teams will enter their cost and resource data directly into an online data collection form. Data entry will be followed by a short interview to clarify unclear values and missing data. A cost report will be generated for each trial, which is then reviewed by the trial team. Funders of RCTs were not contacted, since previous research has shown that budgets are purposefully underestimated and we wanted to record the actual costs of RCTs [35].

For the collection of the resource use and cost data, we will use a previously developed and tested cost item list developed by Speich et al. that follows principles of activity-based costing [27, 36]. An overview of the collected variables can be found in Table 1. All variables and the online data collection form can be found in the supplementary material (Supplement Table 1 and Supplement Table 2). The online cost report form will be tested on two RCTs and changes will be made based on the feedback provided by investigators and study teams.

**Table 1 Tab1:** Total trial costs

**Total Trial Costs ** • Trial Budget • Trial Funding • Total trial costs • Total trial costs adjusted for employer contributions • Total trial costs adjusted for employer contributions and 30% unaccounted time • Total trial costs adjusted for employer contributions, 30% unaccounted time and overhead		
**Planning**	**Conduct**	**Finalization**
**Fixed Costs** • Ethics Committee approval fees • Health authority fees • Other approval fees • Costs for Infrastructure and Equipment • Shipping costs • Insurance fees	**Fixed Costs** • Advertisment • Costs of Intervention • Placebo manufacturing • Additional procedures and material • Patient reimbursement • Specimen analysis • AE/SAE/SUSAR material • Travel costs • Audits and Inspections	**Fixed Costs** • Publication fees • Conference fees and costs
**Variable Costs (in days)** • Research protocol • Budget development • Grants and funding • Application EC, • Patient-related forms • Investigational brochure • Site-specific set-up Staff training • Acquiring study drug • Statistical analysis plan • Data management plan • Monitoring plan • Initial monitoring Visit • Biobank preparation • Communication funders and authorities • Communication involved sites • Communication other stakeholders • Communication patient representatives	**Variable Costs (in days or minutes)** • Screening • Informed consent and patient specific documents • Randomization • Baseline visit • Treatment: intervention • Treatment: control • Sample processing/analysis • Source data and data entry AEs, SAEs and SUSARs • Follow-up/Endline visit(s): • Ongoing communication • Upkeep of documentation • staff training /re-training • Amendments • Audits/ inspections • statistical services • Data management • Monitoring - Upkeep of biobank	**Variable Costs (in days)** • Data cleaning and database lock • Biospecimen storage/destruction • Statistical analyses • Final reporting • Manuscript • Other results dissemination

*Abbreviations*: *AE* adverse event, *SAE* serious adverse event, *SUSAR* serious unexpected serious adverse event, *EC* ethics committee

In short, we will be collecting two types of cost data: Firstly, the fixed costs associated with the trial, which are costs that are independent of time and human resources, such as ethical approval fees, insurance fees, travel costs, and material fees (Table 1). Secondly, we will be collecting variable costs, using a predefined list of study tasks, which are dependent on human resources, time expenditure of the team and salary, such as days needed to write the protocol, days for communication amongst stakeholders, minutes needed for patient screening, recruitment, and treatment (Table 1). Variable costs will be recorded in days or minutes for each study task, for each type of trial team member (principal investigator, site investigator, study nurse/coordinator, senior medical staff, junior medical staff, administrative staff, statistician, IT support and data management, monitor, laboratory staff, or others) and will then be multiplied by their gross yearly income (given by the study team) to calculate billable hours/days. The costs can be entered in five currencies: euro (€), Swiss franc (CHF), pound (£), and US dollar (USD).

From protocols and publications, we will extract the relevant RCT baseline characteristics. These will include medical field (indication), type of intervention and control group, use of placebo, number of arms, type of patient population, specific trial design (e.g., cross-over or factorial design), number of trial arms, number of trial sites, planned and achieved sample size, originally planned total costs and planned budget (if available), primary outcome(s), trial duration, planned and actual recruitment duration, monitoring method, electronic or paper-based data capture/case report forms, and funding sources.

### Sample size considerations

We simulated data sets with various numbers of RCTs to study how many RCTs we would need to achieve a 90% probability (statistical power) for a sufficiently narrow 95% confidence interval (CI) around the estimated mean cost proportions for individual cost items. We assumed that a 95% CI width of 6% (i.e., a maximum of ± 3%) for the estimated mean would be sufficiently precise. The confidence interval assumes a normal distribution and is calculated as 1.96 * the standard error. Figure 1 shows how the required sample size depends on the true average proportion. Note that there are two lines: a dark line for a rather wide assumed distribution of proportions (tau = 10; beta distribution with a precision of 10) and a gray line for a plausible, narrower distribution (tau = 20). According to the dark line (the wider distribution), including a total of 60 RCTs would suffice to achieve a power of 90% to find a satisfyingly narrow 95% CI of 6% for a mean proportion below 0.15. Thus, our original plan was to include at least a total of 180 RCTs which appeared appropriate to achieve sufficient precision for estimated proportions (even within subgroups such as countries). However, it proved extremely challenging to find principal investigators willing to share detailed resource use and cost data of their trials rendering the target sample size of 180 RCTs unfeasible. Therefore, we reduced our target to 100 RCTs (Switzerland *n* = 60; Germany *n* = 20; UK *n* = 20). This number is feasible and will still allow for sufficient precision of unstratified estimates and to conduct multivariable regression analyses without overfitting models.

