## Study objectives and hypotheses

The aim of this study is to generate a database of detailed empirical resource use and cost data from 100 investigator-initiated RCTs in Switzerland, Germany, and the UK, so that we can descriptively investigate total RCT costs and proportions of total costs for individual cost items to achieve the following specific objectives:A)To investigate cost patterns on an absolute (actual costs in USD) and relative scale (% of total costs) including largest cost items for the whole RCT and for the planning, conduct, and finalization phases.B)To explore RCT costs across different strata including medical fields, intervention types, multicenter/single center status, and countries.C)To examine planned versus actual RCT costs and to explore factors that explain excess costs.D)To explore hidden costs associated with conducting an RCT such as resource use and costs for writing the protocol, trial committees, ongoing communication, and managing serious adverse events (SAEs).

We have the following specific hypotheses:(i)The expenses for participant recruitment and follow-up typically constitute the largest proportion of total RCT costs.(ii)Data monitoring constitutes—on average—less than 15% of total RCT costs.(iii)Delays in recruitment of trial participants explains most of the excess costs.(iv)Cost structures (proportions) and fixed cost items (e.g., regulatory or ethics committee approval) are similar across medical fields and countries.

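### Under the plan's wider distribution, 60 RCTs meet the precision target only up to a mean share of about 0.13, and 100 RCTs miss it for mean shares of about 0.33 to 0.67

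*Protocol article*

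**What the plan says.** All of this is in the protocol article, under Sample size considerations, unless stated otherwise.

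- The aim of the simulation was to "achieve a 90% probability (statistical power) for a sufficiently narrow 95% confidence interval (CI") around mean cost proportions. The tolerance is explicit: a "95% CI width of 6% (i.e., a maximum of ± 3%) for the estimated mean would be sufficiently precise". The interval is also defined: "The confidence interval assumes a normal distribution and is calculated as 1.96 * the standard error".
- Two spreads of the proportions across trials are used. The dark line is called rather wide ("tau = 10; beta distribution with a precision of 10"). The other is "a gray line for a plausible, narrower distribution (tau = 20").
- From the dark line the plan concludes that "including a total of 60 RCTs would suffice to achieve a power of 90% to find a satisfyingly narrow 95% CI of 6" per cent, for a mean proportion below 0.15. The target of 180 RCTs is derived from this figure.
- After recruitment proved difficult, the target became 100. The justification is "This number is feasible and will still allow for sufficient precision of unstratified estimates and to conduct multivariable regression analyses without overfitting models".
- Study objectives and hypotheses, hypothesis (i): "The expenses for participant recruitment and follow-up typically constitute the largest proportion of total RCT costs". No numerical share is given.
- Statistical analysis: proportions are to be reported with 95% CIs for individual cost items and for the three study phases.

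**The concern.** For a beta distribution with fixed precision, the spread of shares across trials grows as the mean share moves towards 0.5. A number of RCTs that suffices for a small share therefore need not suffice for a middling one. The plan acknowledges this for 60 RCTs, where it limits the statement to shares below 0.15. It drops the limit for 100 RCTs, where precision is claimed for unstratified estimates in general.

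The sentence is the plan's stated reason why 100 RCTs are enough. If it is too broad, readers will expect every overall proportion to lie within ± 3 points with 90% assurance, including the large ones. Some of the reported proportions are large by construction: the three phase shares add up to 1 in every trial, so at least one phase must average 1/3 or more.

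**Working it through.** **Inputs (Sample size considerations).** Half-width limit 0.03; multiplier 1.96; assurance 90%; shares drawn from a beta distribution with mean p and precision tau = 10 (wider) or 20 (narrower); n = 60 and n = 100.

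**Formulae.**
- Draws: Beta(p·tau, (1 − p)·tau), with SD = √[p(1 − p)/(tau + 1)].
- The criterion is met in a sample if 1.96·s/√n ≤ 0.03, that is, if the sample SD s ≤ 0.03·√n/1.96. This gives s ≤ 0.1186 for n = 60 and s ≤ 0.1531 for n = 100.

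**True SD against that limit.**
- p = 0.15, tau = 10: √(0.1275/11) = 0.1077, limit 0.1186 at n = 60. The margin is about 10%, and s varies from sample to sample by more than that allows.
- p = 0.50, tau = 10: √(0.25/11) = 0.1508, limit 0.1531 at n = 100. There is almost no margin.
- p = 0.50, tau = 20: √(0.25/21) = 0.1091, limit 0.1531 at n = 100. The margin is ample.

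**The plan's own figure first: n = 60, tau = 10** (simulation, 200,000 samples per point, simulation error about 0.1 percentage point).

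| Mean share | 0.13 | 0.134 | 0.136 | 0.14 | 0.149 | 0.15 |
|---|---|---|---|---|---|---|
| P(half-width ≤ 3 points) | 92.1% | 90.6% | 89.7% | 87.9% | 83.2% | 82.6% |

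The 90% holds up to about 0.135, so about 0.13 as a safe rounding. At 0.15, n = 64 gives 89.9% and n = 65 gives 91.1%.

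Other readings of the calculation at p = 0.15 and n = 60 do not restore 90% either: a t quantile gives 77.5%, an SD with divisor n gives 84.9%, and a variance of p(1 − p)/tau gives 69.3%. A normal-theory chi-square shortcut, which is not the beta simulation described, gives 87.3% and reaches 90% at n = 62.

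**The reduced target: n = 100, tau = 10.**

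| Mean share | 0.15 | 0.30 | 0.32 | 0.325 | 0.35 | 0.40 | 0.45 | 0.50 | 0.60 | 0.68 | 0.70 |
|---|---|---|---|---|---|---|---|---|---|---|---|
| P(half-width ≤ 3 points) | ~100% | 94% | 91% | 89.9% | 84% | 73% | 64% | 61% | 73% | 91% | 94% |

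At 0.50 the mean half-width is 2.95 points and its 90th percentile 3.18 points. About 112 RCTs would give 90% there (90.2%).

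**n = 100, tau = 20.** The probability is practically 100% even at 0.50.

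**Where middling shares arise.** The mean phase shares sum to 1. Either one phase averages above about 0.68, in which case the other two lie below 0.32 and all three meet the criterion, or at least one phase lies between 1/3 and about 0.68 and, under tau = 10, misses it. This takes the plan's item-level distribution to apply to phases as well, which is an assumption.

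**The case against.** The case for leaving the text alone has real force on size.

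- **The 60-RCT figure no longer drives the design.** The plan says below 0.15, the boundary is the worst point, the gap is four to five RCTs, and the value was read from a figure that is not available here. With 100 RCTs a share of 0.15 is covered with practical certainty, so hypothesis (ii) on monitoring is untouched. All of this stands. It makes the error small but does not make the figure right: at 0.149, inside the stated range, the probability is still 83%.
- **The plan calls tau = 20 plausible and tau = 10 rather wide.** Under tau = 20 the 100-RCT sentence is true for every share. This stands too. But the plan took its 60-RCT figure from the wider line, and the reduced target should be judged on the same line or the change of assumption should be stated.
- **The criterion was set for individual cost items.** No document shows a single item near 0.5. This is fair, but the claim for 100 RCTs covers unstratified estimates without restriction, and these include the phase shares.

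A reader might infer stronger conclusions that the document does not support:

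- *That 100 RCTs give only 61% for hypothesis (i).* The 61% belongs to a mean of exactly 0.50, and the hypothesis states no share. The Background reports that personnel costs for enrolment, treatment and follow-up were the majority of spending in two earlier trials, but that aggregate includes treatment, which the hypothesis does not name.
- *That the published intervals for small shares will be too short.* The 1.96 × SE formula is given for the sample size simulation. The Statistical analysis section names no interval method.
- *That the overfitting half of the sentence is false.* Nothing in the document shows overfitting at roughly 8 to 10 RCTs per model parameter.
- *That the effective sample is 80 after setting aside pilots and trials in low- and lower-middle-income countries.* The Statistical analysis section says that no collected data will be excluded.

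**Conclusion.** Wrong as written, but minor. Two statements miss the plan's own criterion of 90% probability for ± 3 points under tau = 10:

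1. The 60-RCT statement holds for mean shares up to about 0.13, not 0.15.
2. The precision claimed for 100 RCTs holds for mean shares up to about 0.32 or above about 0.68, not for all unstratified estimates.

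The largest shortfall is 61% instead of 90%, at a share of 0.50. In interval width this is about 0.2 points (3.2 against 3.0 at the 90th percentile), which would hardly affect a descriptive ranking of cost items. The result rests on the simulation as the section describes it. The curve in Figure 1 could not be inspected. Whether a reported share falls in the middle range depends on data not yet reported: it is likely for at least one phase unless a single phase dominates, and possible but unquantified for the category in hypothesis (i).

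**What to change.** Two wording changes in Sample size considerations:

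- In the 60-RCT sentence, change the limit from 0.15 to about 0.13, or keep 0.15 and change 60 to about 65.
- Replace the precision claim for the reduced target with a bounded one, for example: *With 100 RCTs and tau = 10, the 90% probability of a CI within ± 3 points holds for mean proportions up to about 0.32 (or above about 0.68); near 0.5 it is about 61%, with a half-width within ± 3.2 points with 90% probability; with tau = 20 it holds for all proportions.*

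The only cost is a slightly less favourable precision statement. No further RCTs, data or change of analysis are needed.

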**Fig. 1 Fig1:**
[figure not shown]
The required sample size (on the y-axis) required to achieve, with a probability of 90%, an estimate of the mean item cost proportion that has a confidence interval (CI95) smaller than ± 3%, as a function of the true mean item cost proportion (on the x-axis). The different lines represent different assumptions about the distribution of cost proportions across studies

## Data management

All data will be collected for each of the RCTs and the cost data will be collected and stored in the electronic data capture system REDCap [33, 34]. For the statistical analysis, we will transfer data to the statistical software R version 3.5.1.

The variable costs will be adjusted for employer contributions (%), the overhead of the sponsor institution (%), and for unaccounted time (%). Employer contributions are additional expenses and contributions associated with employing a person, such as social security contributions, pension contributions, health insurance, and other benefits that are part of an employee’s compensation package in addition to their base salary; specifically, 23.3% of the gross salary in Germany [37], 15.0% in Switzerland [38], and 21.3% in the UK [39]. Unaccounted time is defined as the time spent on study activities not recorded or accounted for by the study team and was determined as 30%, based on results of a study shadowing clinical investigators during their study activities [40]. The overhead for the institution was recorded in the online data collection form by the study team. All costs will be converted into USD using historical exchange rates provided by the European Central Bank [41]. We will use the start date of recruitment as the date for the historical exchange rate and convert the costs to values for the year 2022. Values will also be adjusted for inflation to the year 2022 using the World Bank inflation index [42].

In Switzerland, a workday was defined as 9.6 h for medical staff (principal investigator, site investigator, medical staff junior, medical staff senior) and 8.4 h for other staff members (research coordinator, statistician, IT support and data management, monitor, laboratory staff), with a total of 226 workdays per year (average number of workdays in Switzerland). In Germany and the UK, a workday was defined as 9.6 h for medical staff and 7.5 h for other staff members, with a total of 223 workdays per year in Germany and 224 work days per year in the UK.

### Statistical analysis

We will calculate proportional contributions to total costs for individual cost items and for the three pre-defined study phases (preparation, conduct, and finalization). Proportions across RCTs will be summarized with descriptive statistics accompanied by 95% CIs. We will summarize total resource use (working hours and costs), as well as resource use and costs for individual cost items, and costs per patient using descriptive statistics (means or medians accompanied by standard deviations (SDs) or 25th to 75th percentile ranges [IQRs] according to the distribution, minimum [min] and maximum [max], respectively) overall and stratified by RCT over- or under-budget (± 10%), medical field, intervention type, country, and pilot vs non-pilot RCTs (objectives A–D).

We will categorize reasons for going over- or under-budget as reported by trial investigators and reasons for prolongation of recruitment [43] (objective C). In sensitivity analyses, we will calculate results without adding 30% of unaccounted time and/or adding overhead costs. We will not exclude any collected data from planned analyses. Outliers will be reviewed and checked/verified with principal investigators of included trials.

We will conduct two multivariable linear regression analyses with total costs in US dollars and total costs per patient as dependent variables [44]. Medical field, country, number of trial sites, actual sample size (only in regression model for total costs), routine data use, intervention type, and actual trial duration will be used as independent variables in both regression analyses. As for the investigation into the strata of cost proportions of RCTs across medical fields, intervention types, and countries, we will first plot distributions of cost proportions graphically stratified by medical field, intervention type, and country. For each RCT, we will descriptively compare the originally planned versus actual total costs, the originally planned versus actual recruitment duration, and the planned versus actual sample size (objective C).

We will calculate excess costs for each RCT (delta of originally planned total costs and actual total costs [Total costs − Planned Costs]). This will help investigate trial characteristics associated with excess costs of an RCT (dependent variable). We will develop a multivariable regression model with delta in recruitment duration, actual sample size, and actual number of trial sites, country, intervention type, and medical field as independent variables (objective C).

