## Background

Randomized clinical trials (RCTs) are the cornerstone of reliable evaluation of interventions in health care, with results that often impact clinical guidelines and evidence-based practice ultimately leading to better health care for patients [1–3]. However, conducting high-quality RCTs is challenging, resource intense, and associated with high costs [4, 5]. Tens of billions of dollars of public and private money are invested in RCTs every year, estimated to reach $68.9 billion a year by 2025 [6]. Moreover, RCT costs are rising. Over the last decade, a number of new initiatives and regulations were implemented to increase participant protection and to improve research quality [2, 7–10]. As a consequence, the complexity and administrative burden of RCTs have increased overall costs [11–15]. Furthermore, the implementation of medical advances, while highly desirable, has limited the incremental impact of new therapies, resulting in smaller beneficial effects of interventions, which requires larger RCT sample sizes [16, 17]. All these developments have resulted in escalating RCT costs, thus exasperating the problem of scarce resources for academic clinical research.

One consequence of these cost pressures is that the number of independent investigator-initiated RCTs has remained constrained over the last two decades [2, 18, 19] and a substantial proportion of these trials are prematurely discontinued due to recruitment and organizational problems [19], which risks many clinical research questions remaining unaddressed. Therefore, efforts to make investigator-initiated RCTs more cost-effective and sufficiently funded are urgently needed.

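### Excess cost and the ±10% budget strata ignore the share of planned patients delivered, so a recruitment shortfall can hide an overrun and mask the cost of delay

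*Protocol article*

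**What the plan says.** The Statistical analysis section of the protocol article summarises resource use, item costs and costs per patient "overall and stratified by RCT over- or under-budget", with a margin of ±10%. It defines excess cost for each RCT as the "delta of originally planned total costs and actual total costs", that is, total costs minus planned costs. Excess cost is then the dependent variable in a "multivariable regression model with delta in recruitment duration, actual sample size, and actual number of trial sites", together with country, intervention type and medical field.

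Planned sample size enters the analysis in one place: for each RCT, planned and actual values of cost, recruitment duration and sample size are compared descriptively. The same section also categorises the reasons that investigators give for going over or under budget, and it excludes no collected data. Planned and achieved sample size and, where available, planned cost are on the extraction list under Data collection procedures.

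Two statements elsewhere bear on the point. The Background says of investigator-initiated RCTs that "a substantial proportion of these trials are prematurely discontinued due to recruitment and organizational problems". Hypothesis (iii) under Study objectives and hypotheses expects recruitment delay to explain most of the excess cost.

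**The concern.** A trial that enrols fewer patients than planned avoids part of its screening, consent, visit, treatment and follow-up costs, all of which Table 1 lists under conduct. Hypothesis (i) expects recruitment and follow-up to be the largest part of total cost, so the saving need not be small. The total then falls for a reason that has nothing to do with budgeting or economy, and this fall can offset a real overrun on the patients who were enrolled.

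Two results under objective C are exposed. First, the on-budget and under-budget strata can mix trials that delivered their plan for the money with trials that delivered much less for it. Second, a model with actual sample size alone cannot tell a trial that enrolled 200 of 200 from one that enrolled 200 of 400. If delayed trials also tend to fall short, the savings from shortfall are credited to delay, and the delay coefficient is pulled down. That coefficient is the one that bears on hypothesis (iii).

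**Working it through.** The plan states no figure for this point, so there is none to reproduce. The definitions come from the Statistical analysis section. The documents give no size-independent cost share, no distribution of shortfall and no overrun, so all values below are assumptions.

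**1. Overrun hidden in an on-budget trial.** Let *s* be the share of planned cost that does not depend on sample size and *a* the achieved/planned sample size. The expected cost of what was delivered, relative to plan, is *s* + (1 − *s*)·*a*.

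- *s* = 0.4, *a* = 0.6: 0.40 + 0.60 × 0.60 = 0.76.
- Spending exactly the plan (on budget): 1/0.76 − 1 = 32% above the expected cost.
- Spending 0.85 of plan (under budget): 0.85/0.76 − 1 = 12% above.
- Range for spending exactly the plan: *s* = 0.6, *a* = 0.8 gives 0.92 and 1/0.92 − 1 = 9%; *s* = 0.3, *a* = 0.6 gives 0.72 and 1/0.72 − 1 = 39%.

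**2. Where a short trial lands.** Let *g* be the overrun on patient-dependent cost. Actual/planned cost is *R* = *s* + (1 − *s*)·*a*·(1 + *g*).

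| *a* | *g* | *s* | *R* | Class |
|---|---|---|---|---|
| 0.7 | 0 | 0.4 | 0.82 | under |
| 0.7 | 0.5 | 0.2 | 1.04 | within ±10% |
| 0.7 | 0.5 | 0.8 | 1.01 | within ±10% |
| 0.8 | 0.5 | 0.2 | 1.16 | over |
| 0.8 | 0.5 | 0.4 | 1.12 | over |
| 0.9 | 0.3 | 0.2 | 1.14 | over |

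At 70% of target, a 50% overrun on patient-dependent cost stays within ±10% for *s* from 0.2 to 0.8. At 80–90% of target, a short trial can still be classed as over budget. The offset is possible, not automatic.

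**3. The excess-cost model.** Simulation of 100 trials, repeated 500 times. Assumed: achieved/planned sample size around 0.85 (SD 0.2), delay longer where the shortfall is larger, 3000 per patient, 300000 fixed, and a true delay cost of 8000 per month.

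- Excess cost on delay and actual sample size: mean delay coefficient about −2300.
- With planned sample size added: about 8020.

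The reason is algebraic. Excess cost contains the per-patient cost times (actual − planned sample size). With planned sample size left out, that term is absorbed by whatever correlates with shortfall, here delay. The size and even the sign of the first coefficient depend on the assumed values; the downward direction follows from delay and shortfall going together.

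**4. Why a plain per-patient ratio is not the remedy.** With no overrun at all, actual over planned cost per patient is *s*/*a* + (1 − *s*). For *s* = 0.4, *a* = 0.7 this is 0.4/0.7 + 0.6 = 1.17; for *s* = 0.6, *a* = 0.7 it is 0.6/0.7 + 0.4 = 1.26. The ratio passes 1.10 on shortfall alone, because size-independent cost is spread over fewer patients.

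**The case against.** Objective C asks about planned versus actual cost, and total minus planned answers exactly that. A trial that spends its plan is on budget in the ordinary sense, whatever it recruited. The plan also does not ignore delivery: it summarises cost per patient within the budget strata, categorises the reported reasons for budget deviations, compares planned and actual sample size for each RCT, and adjusts for actual sample size. The sample is restricted to completed or nearly completed trials, and the Discussion concedes that it may favour more successful ones, so the Background remark on discontinuation gives no shortfall rate for this sample.

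Much of this stands. The crude difference is a legitimate result and should stay. A reader might infer that trials which missed their target are simply counted as on or under budget, or that the share of trials over budget is understated. The documents support neither. Short trials can also land over budget, and the second inference holds only if over budget is redefined as above the planned cost of the patients delivered. Nor does the article say that the under-budget group will be read as economical.

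What remains is narrower. Cost per patient by stratum has no planned counterpart, reported reasons do not alter the classification, and actual sample size without planned sample size carries no information on shortfall. The article itself fixes the definition, the strata and the covariates, so this is not a detail left to an analysis plan that is not shown.

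**Conclusion.** The point holds in a limited form. A recruitment shortfall can offset an overrun in the ±10% classification and in excess cost, and it can bias the delay coefficient that bears on hypothesis (iii). For a trial that spends exactly its plan, the hidden overrun is 32% in the central illustration and 9–39% over the stated range. These figures rest on assumed cost shares and attainment and on cost that is linear in patients. The masking of delay further assumes that delayed trials tend to be short of target. How many of the 100 trials would be affected cannot be computed from the documents. This is an inexpensive improvement to the interpretation of objective C, not an error in the planned-versus-actual comparison itself.

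**What to change.** - Keep total minus planned cost, and the ±10% strata built on it, as the planned-versus-actual result.
- Cross-tabulate or split the budget strata by whether at least 90% of the planned sample size was reached.
- In the excess-cost model, add planned sample size beside actual, or add achieved/planned sample size. The simulated figure above is for planned sample size, which fits a difference in dollars most directly.
- Planned and actual cost per patient may be shown descriptively, with a note that their ratio rises with shortfall even without overspend. Do not base statements about efficiency on it.

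No new data are needed: planned and achieved sample size and planned cost are already on the extraction list, and actual cost is collected. The price is thinner strata and one more covariate, in a subset already reduced because budgets are recorded only where available and the Missing data section plans complete-case analysis for them.
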